### Inclusion and Exclusion Criteria

Participants will be screened for the following eligibility criteria: (1) are aged at least 18 years, (2) self-identify as Indigenous to North, South, Central Americas, or the Caribbean, and (3) live in New York State. Individuals are not eligible if they live outside of New York State, do not self-identify as Indigenous, or are less than 18 years of age. Practitioners will be screened for the following eligibility criteria: (1) are a mental health professional licensed to practice in New York State and (2) self-identify as Indigenous to North, South, or Central America or the Caribbean.

### Data Safety and Monitoring

The study facilitator, under the supervision of the principal investigator, will monitor data. Data will be securely stored on a password-protected computer, laptop, and on a password-protected Google Drive associated with the study facilitator’s university-administered email address. Hard-copy data will be stored in a securely locked filing cabinet in the study coordinator’s office, to which only the study facilitator will have access. All data collection will be entirely anonymous; no identifiers will be associated with the ID number labeled on the data.

### Potential Risks

Despite best efforts to protect privacy and confidentiality, participants face a risk of potential loss of confidentiality. During the health care provider focus group, there is a potential for loss of confidentiality, although all participants are asked to keep their involvement in the study and what is shared during the focus group private. During an in-depth interview, there may be risks associated with discussing potentially stressful subjects. There is no more than a minimal risk of any harm to participants.

### Potential Benefits

Participants may benefit from increased access to a culturally relevant mental health therapist. Some participants may find the in-depth interview process empowering and therapeutic in experience. Additionally, the information collected from this research may help others in the future.

### Ethical Considerations

This study has been approved by the Columbia University Institutional Review Board (AAAU0850). The study coordinator will contact client and practitioner participants to determine their eligibility and to discuss the study purpose, risks, benefits, and compensation. During this meeting, the study coordinator will also obtain informed consent. Participants will be provided with an electronic version of the consent form and will be asked to sign and return the form at the end of the call.

Participants will be informed that they can opt out at any point during the study. Data will be anonymized, and no names or other identifiable features of research participants or users will be disclosed in any manuscript or supplementary material.

Participants (therapy seekers) will be compensated US $10 for completing each survey, one at baseline and one at 3 months follow-up. Participants (therapy seekers) will receive US $30 for completing an in-depth interview. In total, participants are eligible to receive a total of US $50 for completing both surveys and the in-depth interview. Additionally, as a part of participating in this study, participant clients will have the cost of their therapeutic sessions covered, up to 5 sessions and no more than US $600. Therapist participants will be compensated with US $40 for completing the focus group session.

### Dissemination

Initial findings will be disseminated first to participants to obtain their feedback and to ensure that the themes that are developed from the qualitative interviews align with their experience and accurately represent their views. Additionally, results from this study will be disseminated in culturally relevant and accessible ways, such as community meetings, social media posts, and a community-facing report that will be developed with ShockTalk. Findings will be used to improve the current ShockTalk app and linkage-to-care process. The results will also be used to facilitate the search for additional sources of funding to implement broader assessments.

### Measures

#### Quantitative Measures

The first survey instrument will examine changes in attitudes related to tele–mental health treatment value for clients before and after treatment facilitated by ShockTalk. One month before treatment and 3 months after treatment, clients will be given the Attitudes Toward Seeking Professional Psychological Help-Short Form survey [24]. This survey measures participants’ openness to seeking professional help for emotional problems and the value and need for seeking professional help. Clients are asked whether they disagree, partly disagree, partly agree, or agree with an item, including questions such as, “The idea of talking about problems with a psychologist strikes me as a poor way to get rid of emotional conflicts” and “A person with an emotional problem is not likely to solve it alone; he or she is likely to solve it with professional help.” Their attitudes toward seeking professional help are scored based on the sum of all responses. The short version of the scale demonstrates internal consistency ranging between 0.82 and 0.84, and high test-retest reliability (a=0.80) [24]. Once the presurveys and postsurveys are collected, the study team will examine the differences in openness to treatment before and after ShockTalk*.* A positive difference between the pretreatment and posttreatment Attitudes Toward Seeking Professional Psychological Help-Short Form score will indicate an increase in client valuation of mental health care treatment. *t* tests (1-tailed) will be used to evaluate whether the differences are statistically significant.

The second survey addresses trust and accessibility in tele–mental health care services and linkage services for clients. Clients will be asked 5 items each from the Trust in Technology and Trust in Telemedicine Service scales from the Patient Trust Assessment Tool (PATAT) [25]. The PATAT is a trust benchmarking survey and, currently, the only instrument that provides a comprehensive measurement of trust in an eHealth service and the underlying trust concepts. Clients will respond to questions related to their trust in technology and telemedicine surveys using responses on a Likert scale, which ranges from totally disagree (1) to totally agree (5). Questions from the Trust in Technology subset include items such as “Everything done on ShockTalk remains private” and “The personal information that is stored at ShockTalk will not get lost.” Items from the Trust in Telemedicine Service include questions such as “I trust ShockTalk less than other online services.” In conjunction, these 2 quantitative surveys will assess practitioner and client trust in the ShockTalk app and changes in client valuation of treatment resulting from culturally appropriate telehealth care linkage.

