## Methods

### Overview

To test the feasibility of ShockTalk among Indigenous clients, we will conduct a small pilot study with 10 Indigenous therapy-seeking clients and 3 Indigenous mental health practitioners in Lenapehoking. This study was designed as a preliminary feasibility pilot to inform a larger trial and, therefore, was not prospectively registered.

After informed consent and baseline assessment, clients will be randomly allocated 1:1 to immediate access to ShockTalk (treatment) or to a 3-month waitlist control (5 clients per arm). The allocation list will be generated by a study team member not involved in enrollment and uploaded to a centralized randomization module, which will reveal the assignment only after baseline data entry. Allocation events will be logged. In the absence of a centralized system, sequentially numbered, sealed opaque envelopes prepared from the same allocation list will be used.

All participants will complete baseline surveys and a 3-month follow-up survey (3 months postrandomization). Waitlist participants will be offered access to the linkage-to-care intervention 3 months after their initial baseline survey is completed. Qualitative data collection at 3 months from baseline will include 1-hour semistructured interviews (Multimedia Appendix 1) with a purposive subsample of 5 clients (selected to reflect a range of engagement and experiences across arms) and a single focus group with participating practitioners. Finally, a preliminary cost analysis will be conducted using data from both arms to assess the feasibility of cost data collection and to generate exploratory cost estimates across varying levels of engagement. Analyses will be descriptive and feasibility-focused (ie, recruitment, retention, acceptability, and data completeness); inferential effectiveness claims will not be made given the pilot sample size.

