#### Quantitative Analysis

Quantitative analysis will involve linear mixed-effects models to understand the impact of different treatment doses on mental health outcomes, accounting for repeated measures and potential intragroup correlations. ANOVA will be used to compare the mean outcomes across the dose groups. Because of sample size limitations, we acknowledge that *t* tests and ANOVA may be underpowered to detect the true impact of the intervention on changes in attitudes surrounding therapy. In tandem with the cost analysis, the ANOVA will provide insights into the optimal balance between treatment effectiveness and cost, guiding resource allocation and decision-making for culturally responsive mental health services delivered through the ShockTalk app.

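### Clients are randomised to immediate access or waitlist, but no stated outcome analysis compares the arms, and the planned tests and causal wording contradict the plan's own disclaimer

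*Protocol article*

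**What the plan says.** **Design (Methods, Overview).** After baseline assessment, "clients will be randomly allocated 1:1 to immediate access to ShockTalk (treatment) or to a 3-month waitlist control (5 clients per arm"). On follow-up: "All participants will complete baseline surveys and a 3-month follow-up survey (3 months postrandomization"). On the control arm: "Waitlist participants will be offered access to the linkage-to-care intervention 3 months after their initial baseline survey is completed". At the 3-month survey the waitlist arm is therefore a concurrent, unexposed comparison group.

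**Outcome analyses.**
- Quantitative Measures: for the ATSPPH-SF, "the study team will examine the differences in openness to treatment before and after ShockTalk", and t "tests (1-tailed) will be used to evaluate whether the differences are statistically significant".
- Cost Analysis: outcomes described by number of sessions completed (examples 1-2 and 3-5), with no inferential comparison between those groups.
- Quantitative Analysis: "linear mixed-effects models to understand the impact of different treatment doses on mental health outcomes", plus ANOVA across the dose groups.
- Patient Trust Assessment Tool (PATAT): no separate contrast is given.

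**Attribution.** Quantitative Measures says the two surveys will assess "changes in client valuation of treatment resulting from culturally appropriate telehealth care linkage". Quantitative Analysis describes the t tests and ANOVA as possibly too weak to detect the intervention's real effect on attitudes.

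**Disclaimer.** The Overview says the analyses are descriptive and centred on feasibility, and rules out inferential claims of effectiveness because of the pilot's size.

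**The concern.** The plan sets up a randomised waitlist and then states outcome contrasts that do not use it as a control. A before/after difference contains whatever would have happened anyway: drift in attitudes over three months and the effect of answering the same questionnaire twice. The waitlist arm is there to remove these. The dose contrasts do not replace it, because sessions completed is chosen by the client after randomisation and the example strata include no zero-session group.

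This is not detail that an article leaves to a fuller document. The article does state a contrast, a test and a direction, and it then describes the resulting change as produced by the linkage. Limitations and Future Research says the findings will feed sample-size calculations for a later randomised trial. If an effect estimate is carried forward for that purpose, a pre/post mean change is not the quantity a randomised comparison would estimate.

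**Working it through.** The documents give no alpha, SD, effect size or power, so there is no figure to reproduce. The check has three parts.

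**1. Count of stated outcome contrasts.**

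| Contrast | Where | Number |
|---|---|---|
| Before/after | Quantitative Measures | 1 |
| By dose (descriptive strata, mixed model, ANOVA) | Cost Analysis; Quantitative Analysis | 3 |
| Between randomised arms | none | 0 |

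The Overview mentions the arms in only two other ways: for choosing interviewees, and as a source of cost data across engagement levels.

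**2. Which survey counts as after treatment for a waitlist client?** Quantitative Measures ties the surveys to treatment: "One month before treatment and 3 months after treatment, clients will be given the Attitudes Toward Seeking Professional Psychological Help-Short Form survey". The Overview ties them to randomisation. A waitlist client gets access at month 3.
- On the Overview's schedule, the second survey (month 3) comes before any exposure.
- On the treatment-based schedule, it falls at month 3 + 3 = 6 at the earliest. The Overview schedules no survey then, and Ethical Considerations pays for only two surveys, at baseline and 3 months.

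The Abstract's Methods paragraph adds a third description: 5 clients admitted first and 5 more at 3 months. The plan therefore does not settle whether waitlist change enters the before/after contrast.

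**3. Illustration of the drift problem.** Assumptions, none from the documents: one-sided alpha 0.05, normal change scores with SD 1, zero true effect, and drift d common to both arms.

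Rejection probability of the pre/post t test = 1 − F(t[0.95, n−1]), where F is the noncentral t distribution with n−1 df and noncentrality d√n.

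| d (SD of change) | n=5 (one arm) | n=10 (only if all pooled) |
|---|---|---|
| 0.3 | 14% | 22% |
| 0.5 | 24% | 43% |
| 0.8 | 44% | 75% |

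In a between-arm t test of change, common drift cancels. Simulation with 200,000 runs at 5 v 5 gave 4.98% at d = 0.5 and 4.99% at d = 0.8.

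Precision of the between-arm estimate at 5 v 5, unadjusted: half-width of the two-sided 95% CI = t[0.975, 8] × √(1/5 + 1/5) = 2.306 × 0.632 = 1.46 SD. The difference detectable with 80% power is 1.72 SD one-sided or 2.02 SD two-sided. This is why an estimate with an interval is appropriate and a test is not.

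With the 4 clients reported under Results, a baseline-adjusted model has 3 parameters (intercept, arm, baseline) and leaves 4 − 3 = 1 residual df.

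**The case against.** The strongest defence is that this is a feasibility pilot that says so. The Overview disclaims effectiveness inference, Study Sample Recruitment says the size is pragmatic, Quantitative Analysis admits low power, and Limitations and Future Research says significance cannot be established with 10 participants. This stands as a limit on the harm. It does not remove the problem, because the same article still specifies significance tests and attributes the change to the linkage.

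A second defence is that the Abstract's staggered-admission wording may describe the design actually run. In that case a concurrent 3-month contrast may not exist and before/after would be the natural analysis. This also stands, and it makes any between-arm remedy conditional on reconciling the two descriptions.

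Three stronger readings are tempting but not supported:
- **Dilution by pooling.** A reader might infer that unexposed waitlist change is pooled with treated change, so that a 1.0 SD effect appears as 1.0 × 5/10 = 0.5 SD. No section says the arms are pooled, and under the treatment-based survey timing every client in the contrast would have been treated.
- **A single headline error rate.** The 43% figure needs pooling, one chosen drift value and an unstated alpha. Only a range under declared assumptions is defensible.
- **Regression to the mean as a source of false benefit.** Eligibility is by age, identity and residence, with no attitude threshold. If therapy-seekers start with favourable attitudes, regression would lower scores.

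**Conclusion.** The point holds in a limited form. As written, no outcome analysis compares the randomised arms. The one analysis of the attitude score is a one-tailed before/after test that cannot separate ShockTalk from drift or repeat-survey effects. The tests in Quantitative Measures, and the attribution there and in Quantitative Analysis, contradict the Overview's disclaimer.

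Under the stated assumptions (drift 0.3 to 0.8 SD, one-sided alpha 0.05), spurious significance occurs in about 14% to 44% of trials with 5 clients, against about 5% for an arm comparison. The 22% to 75% range applies only if all 10 clients are pooled. The actual drift is unknown, so these figures show the mechanism and do not predict a result. A reader might conclude that the trial will make an invalid effectiveness claim. The plan rules out such claims, so this should be fixed but does not invalidate the pilot.

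**What to change.** 1. Reconcile the design and survey timing across the Abstract's Methods paragraph, the Overview and Quantitative Measures, and state which was run.
2. If it was the Overview's design, replace the one-tailed before/after t test with a descriptive between-arm difference in 3-month ATSPPH-SF, adjusted for baseline, with a two-sided 95% CI and no test. Show within-arm change separately by randomised arm.
3. Describe the PATAT by arm only where clients without access can meaningfully answer items that name ShockTalk.
4. Label the dose comparisons in Quantitative Analysis as non-randomised and descriptive.
5. Remove the wording in Quantitative Measures and Quantitative Analysis that attributes change to the intervention.
6. With 4 clients enrolled, and their split by arm not given, use no model-based inference. Report change by arm only in a form consistent with the confidentiality priority in Limitations and Future Research. An open listing of individual values could conflict with it.

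**Cost.** A few lines of analysis and reporting text, and no new data if the Overview's survey schedule was followed. The price is a very wide interval (half-width about 1.46 SD even at the planned 5 v 5, unadjusted) and some disclosure risk with so few clients.

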#### Qualitative Measures

To identify potential service gaps or accessibility concerns in the ShockTalk app, we will conduct in-depth interviews with the practitioners and clients 3 months after treatment participation. Practitioners will be interviewed in a talking circle, a technique consistent with Indigenous methodologies [26]. In the talking circle, practitioners will be asked a series of open-ended questions related to their past experiences with telehealth care linkage systems and how ShockTalk compares with other systems in terms of accessibility, organization, and usability. They will also be asked about their favorite elements of the app, any problems they experienced, and potential improvements that might benefit both the client and the practitioner. The qualitative interview consists of 6 base questions with several probing questions. The talking circle is expected to take 1 to 2 hours.

Clients will also engage in one-on-one in-depth interviews. Although talking circles may be preferable to facilitate discussions, the sensitive nature of the client interviews prevents the study team from conducting discussions of this type. Clients will be asked about their previous experiences in therapeutic contexts, how their experience in therapy resulting from ShockTalk is similar to or different from those experiences, and what could be done to make the app more accessible. Clients are asked to walk through the process of accessing ShockTalk and discuss points at which the app was not intuitive or was problematic. After discussing the process and experience of using the app, clients will be asked about their process in choosing and retaining a therapist—what therapist attributes were most important in deciding on a therapist, what factors influenced a therapeutic fit, and what influenced their likelihood of rescheduling with the therapist they saw. Finally, clients are asked about any potential changes or improvements they would make to improve their experience. Each client interview is expected to take 30 minutes to 1 hour.

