**Methods:**

This study outlines the development and pilot study of ShockTalk. The conceptual framework is based on the behavioral model of health care use. ShockTalk uses artificial intelligence to connect clients with Indigenous or culturally aligned therapists and facilitates access to care via Facebook Messenger. Using a prewaitlist or postwaitlist design, 5 client participants will be admitted to the study at first, and 5 additional participants at 3 months. Data collection includes presurveys and postsurveys on client attitudes toward mental health treatment and trust in the ShockTalk platform at baseline and a 3-month follow-up, followed by in-depth qualitative interviews at 3 months. A preliminary economic evaluation will track direct costs (ie, therapist time, platform fees, and administrative expenses) and compare relative costs across treatment doses. Analyses will assess the feasibility of data collection and inform a future full-scale trial.

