### ShockTalk App: How It Works

ShockTalk (Figure 2) is a mobile app that uses Facebook Messenger as its entry point for clients. When a client first connects, they are greeted by ShockTalk’s artificial intelligence (AI) assistant, which guides them through the initial process. The AI collects basic contact information, helps synchronize important dates directly to the client’s calendar, and offers an option to schedule a 15-minute intake session with a licensed therapist from ShockTalk’s vetted health care provider directory.

Before the intake appointment, the AI sends reminder messages to help clients prepare. During the intake, the therapist and client discuss needs, goals, and preferences. Together, they decide whether the therapist is a good fit for ongoing care. If so, they begin a therapeutic relationship within the platform. If not, the therapist helps connect the client to other appropriate services or health care providers.

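### Two timing rules conflict: the Measures sections time the attitude survey and interviews from treatment, the Overview from randomization or baseline, and following Measures would select on successful linkage

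*Protocol article*

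**What the plan says.** The protocol article gives two schedules for the same assessments.

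**Timed from treatment**
- Quantitative Measures, on the Attitudes Toward Seeking Professional Psychological Help-Short Form (ATSPPH-SF): "One month before treatment and 3 months after treatment, clients will be given the Attitudes Toward Seeking Professional Psychological Help-Short Form survey".
- Qualitative Measures, in the sentence that gives service gaps and accessibility problems as the purpose of the interviews: "we will conduct in-depth interviews with the practitioners and clients 3 months after treatment participation".

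**Timed from randomization or baseline**
- Methods, Overview, on surveys: "All participants will complete baseline surveys and a 3-month follow-up survey (3 months postrandomization".
- Methods, Overview, on interviews: "Qualitative data collection at 3 months from baseline will include 1-hour semistructured interviews". The sample is 5 clients, "selected to reflect a range of engagement and experiences across arms".
- Abstract, Methods: surveys "at baseline and a 3-month follow-up, followed by in-depth qualitative interviews at 3 months".
- Ethical Considerations: payment for two surveys, at baseline and at 3 months.

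Three other statements bear on the point. The Overview offers waitlist clients access 3 months after their baseline survey. ShockTalk App: How It Works describes an intake that may end without a therapeutic match: "If not, the therapist helps connect the client to other appropriate services or health care providers". Cost Analysis counts dose as completed therapy sessions, and its example strata are 1 to 2 and 3 to 5 sessions, with no level for zero.

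**The concern.** ShockTalk is a linkage app. Its pathway runs from messenger contact to an optional intake booking, the intake, and a joint decision on fit. Starting therapy is therefore the event the app is meant to produce, and it happens after randomization. An assessment dated from that event exists only for clients in whom it occurred.

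Clients who stop at the messenger step, book no intake or are referred elsewhere are the ones who met the access barriers. If they drop out of the interviews, the accessibility evidence loses its most informative cases. If they drop out of the post-survey, the before/after attitude change describes only those who were successfully linked. Accessibility is a stated aim, and the pilot is meant to refine procedures for a larger trial, so the protocol should not leave open which rule governs.

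**Working it through.** No stated figure in the protocol bears on this point, so there is none to reproduce. The check compares the two calendars and then illustrates the possible bias.

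**1. Calendar.** Month 0 is baseline, taken as about the time of randomization. Intervals after treatment are counted from its start, the earliest reading.

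| | Overview | Measures sections |
|---|---|---|
| Immediate arm, linked | Survey and interview at month 3 | If baseline is the survey 1 month before treatment: treatment at month 1, post-survey at 1 + 3 = month 4. If treatment starts at month 0: post-survey at month 3, but the pre-survey falls at month −1, before baseline |
| Immediate arm, never in therapy | Month 3 | No date |
| Waitlist arm, linked | Month 3, about when access is offered | Access at month 3 at the earliest: pre-survey at 3 − 1 = month 2 or later, post-survey and interview at 3 + 3 = month 6 or later |
| Waitlist arm, never in therapy | Month 3, about when access is offered | No date |

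In the waitlist arm the schedules differ by at least 6 − 3 = 3 months. Under the Overview, all 10 planned clients have a survey date. Under the Measures wording, only those who start therapy do. Neither schedule gives a post-offer assessment to a waitlist client who never links.

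**2. Chance that it arises.** The documents give no start rate, so I assume that a share p = 10% to 40% of clients offered access do not start, independently of one another. The chance of at least one non-starter among k clients is 1 − (1 − p)^k.
- k = 5 (planned immediate arm): 1 − 0.9^5 = 0.41; 1 − 0.6^5 = 0.92.
- k = 4 (clients enrolled, per Results, if all were offered access): 1 − 0.9^4 = 0.34; 1 − 0.6^4 = 0.87. Each client lost is then 1/4 = 25% of the data.

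**3. Size if non-starters are dropped.** Let starters change by d and non-starters by 0. The mean among all offered access is (1 − p)d and the starters-only mean is d. Their ratio is 1/(1 − p), whatever d is.
- p = 10%: 1/0.9 = 1.11, an overstatement of 11%.
- p = 20%: 1/0.8 = 1.25, or 25%.
- p = 40%: 1/0.6 = 1.67, or 67%.

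This third step applies only if the Measures rule is followed and the missing clients are left out.

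**The case against.** A reader of the Measures sections alone might infer that clients who never reach therapy have no follow-up at all, and that accessibility and attitude change are judged only on linked clients. The documents do not support that. The Overview sets the follow-up survey for all participants and seeks interviewees with a range of engagement, and the Abstract and the payment schedule agree on the timing. No sentence restricts surveys or interviews to linked clients. This objection stands, and it limits the point to a conflict between rules.

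Four further objections have weight.
- Treatment need not mean therapy. The Overview labels the immediate-access arm as treatment, and on that reading the Measures anchor would be access, which non-starters also have. However, Quantitative Measures speaks of treatment that ShockTalk facilitates, dose is counted in sessions, and part of the interview asks about the therapist the client saw. The usage is mixed. Even on the access reading, the waitlist calendar still conflicts with the Overview.
- The pilot would not be blind to failed linkage. Session attendance and app interaction data do not require a therapy start, clients are asked to walk through the access process, and the timing of the trust survey is not tied to treatment.
- The start rate and the zero change in non-starters are assumptions, and the protocol disclaims effectiveness claims.
- Timing every assessment from the offer of access would move the waitlist post-survey to about month 6. That would lose the concurrent control measurement or add a survey. This rules out the offer of access as the common anchor.

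**Conclusion.** The point holds as an internal contradiction with a consequence. The protocol states two anchors for the ATSPPH-SF and the client interviews and does not say which governs. If treatment means therapy, the Measures anchor conditions on the app's own success and would bias the accessibility and attitude results. The Overview anchor does not, although for waitlist clients it gives only a control measurement at about the time of the offer.

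It would go too far to say that the pilot excludes unlinked clients or cannot show where linkage fails. The Overview schedule and the engagement data contradict both statements. The trust survey is outside the point.

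The size of any bias cannot be derived from the documents. The 11% to 67% range rests on an assumed 10% to 40% not starting, no change in those clients, and their omission from the analysis. The change is worth making because it is cheap and touches a stated aim.

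**What to change.** 1. In Quantitative Measures and Qualitative Measures, adopt the Overview schedule: ATSPPH-SF post-survey at 3 months postrandomization and interviews at 3 months from baseline. State that this applies to every client whether or not an intake or session took place, with interviews still limited to the purposive sample.
2. State that immediate-access clients with no intake or no session are eligible for that sample.
3. Add a zero-session level to the dose description in Cost Analysis.
4. Report attitude change for all clients by randomized arm, with therapy starters as a labelled secondary description.
5. If waitlist clients are to be assessed after access, make this additional to their month-3 control survey, time it from the offer of access, and name it as an extra cost.

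Results states that data collection and analysis are finished. For this pilot, the report should therefore say which anchor was used and how many clients were offered access, had zero sessions, were surveyed and were interviewed. The wording changes then serve the larger trial.

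**Cost.** Items 1 to 4 need a few sentences and no extra visits or instruments. Therapy questions are skipped for non-starters, and the mean change may look less favourable. Item 5 is a third survey beyond the two now paid for. At the protocol's US $10 per survey and US $30 per interview, and assuming the same rates, 5 waitlist clients would cost up to 5 × 10 = US $50 for surveys and 5 × 30 = US $150 for interviews, plus staff time and follow-up beyond the 3-month horizon.
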